# intervention and Control

## Therapeutic Intervention: Body acupuncture

### Acupuncture rationale

#### Style of acupuncture

The intervention in this study is Chinese medicine needle acupuncture delivered in a semi-pragmatic setting (as per usual clinical practice but treating acupuncturists must include acupuncture points from a list provided).

#### Reasoning for treatment provided

Acupuncturists are to perform Chinese medicine diagnosis based on history and examination as per usual clinical practice. The list of points that acupuncturists must select from are based on acupuncture points used in other clinical trials on acupuncture for weight loss in PCOS and also on a textbook and literature review.

#### Extent to which treatment will be varied

In choosing the acupuncture prescription, treating acupuncturists are given the following instructions:

- Treatment of obesity/overweight is the primary objective of the acupuncture treatment
- At least six acupuncture points must be chosen from a list of 17 core acupuncture points that will be provided to the practitioner. These points are chosen from the traditional points that are recommended for treatment of syndromes that are related to obesity and PCOS, and from the points used in previous acupuncture for obesity and PCOS trials.
- Points on the chest or back must be avoided to avoid risk of pneumothorax.
- *De qi* must be obtained for each point using thrusting, twirling and rotating, until the participant reports numbness, heaviness, pressure, soreness or tingling.
- Needles are manipulated after ten minutes (thrusting, twirling and rotating until De qi is reported)
- Needles are withdrawn after 30 minutes

### Details of needling

#### Number of needle insertions per subject per session

A minimum of ten acupuncture needles will be inserted per session.

#### Names of points to be used

The core acupuncture points to be used are ST36, SP6, ST25, ST40, CV12, CV6, LI11, SP9, CV9, CV3, CV4, LI4, KI13, KI7, ST28, LR3, GB34. These points are located on the upper or lower limbs or abdomen. Acupuncture points will be generally needled bilaterally, unless they are midline points, or there are other reasons for unilateral needling for example pain or bruising on one side.

#### Depth of insertion and response sought

Needles will be inserted until *de qi* is obtained. *De qi* is defined as ***numbness, heaviness, pressure, soreness or tingling.***

#### Needle stimulation

A combination of manual and electrical stimulation (electro-acupuncture) will be used. *De qi* must be obtained for each point using thrusting, twirling and rotating, until the participant reports numbness, heaviness, pressure, soreness or tingling. Electro-acupuncture will be applied to ST28 and SP6 bilaterally (4 points, on the lower abdomen and lower leg). Electro-acupuncture is delivered using TGA-approved electro-acupuncture devices that deliver low-frequency electrical pulses to the attached needles (2Hz, 0.3ms, continuous stimulation) and intensity is to be gently increased until a small muscle contraction is seen or felt, but without any discomfort or pain. Acupuncturists are to note down the intensity of the stimulation at each session.

#### Needle retention time

Needles are retained for 30 minutes.

#### Needle type

Needles are stainless steel, sterile and disposable. Acupuncture needles are standard , 32G thickness and 30mm length.

#### Quality control

Each acupuncture practitioner is to take a digital photo of the acupuncture points inserted in order for acupoint location to be verified. This is done once per practitioner, and within the first few treatments provided for the trial. The de-identified photo is to be sent to [name] by text message or email and identified only by ID number and date of treatment, and will be stored on the University’s secure cloud server. No identifying features will be included (such as facial features). Privacy must be maintained by using sheets or blankets to cover any sensitive areas such as the pubic region. Consent from each participant is sought at the time of enrolment.

### Treatment regimen

#### Treatment frequency and duration

Women allocated to the acupuncture group will receive a total of 11 treatments of acupuncture over 12 weeks (twice a week for the first two weeks, weekly for four weeks, then fortnightly for 3 treatments). This tapering schedule is consistent with usual clinical practice. Needles are retained for 30 minutes.

#### Dealing with missed sessions

At the time of enrolment, participants are to be made aware of the nature of their commitment over the twelve week treatment period and encouraged to notify the research office, [name] or the treating practitioner as soon as a break in treatment is foreseen. If treatments are missed, all attempts will be made to complete ten treatments within the eight weeks, providing there is at least a 2 day interval between treatments A break in the intervention schedule may be unavoidable, due to illness or holiday. If the acupuncturist becomes aware that a break of more than two weeks is likely, they will be instructed to liaise with [name] for advice on how to deal with this. [name] or the research assistant will liaise with the participant to determine the cause of missed sessions and will attempt as much as possible to implement appropriate measures to minimise further breaks in between treatments.

As analysis will be by intention-to-treat (that is, all data will be analysed even if a participant has dropped out from the trial), a minimum number of treatment sessions to meet the protocol has not been specified.

### Other components of treatment

Treating acupuncturists may provide diet and lifestyle advice according to Chinese medicine principles. This advice usually consists of advice to avoid ingesting foods that are considered too “hot” or “cold” for the patient’s constitution. However, no additional Chinese medicine treatments will be provided including Chinese herbal medicine, or additional physical or stimulation treatments such as moxibustion or cupping.

Participants will attend for treatment at private clinics of the treating acupuncturists. Treating acupuncturists are advised that they may proceed according to usual clinical practice with the following limitations:

- The acupuncture protocol must be targeted at weight loss as the primary outcome
- The acupuncture protocol must adhere to the standardization applied to acupuncture points, manipulation, stimulation, retention time, frequency as described above
- Only body acupuncture, diet and lifestyle advice (according to Chinese medicine) may be provided.

Practitioners are free to practise as they usually practise. They will be trained to ask about adverse events, and to treat patients warmly and courteously. All efforts will be made to ensure the participants have a comfortable acupuncture experience.

Practitioners will record details of each treatment on an individual Case Report Form which will be kept in a locked cupboard in the clinic and returned to the research team at the end of the study.

### Practitioner background

A minimum of six practitioners have been chosen to administer the treatments. They are have a Bachelor degree in Chinese Medicine, have five or more years of clinical experience and are registered with the Chinese Medicine Registration Board.

Practitioners will receive training from [name], an experienced acupuncture researcher. Training will take place 4-6 weeks prior to anticipated start of recruitment. They will receive a detailed Practitioner Training Manual. Training will be “hands on”. Refresher training will be provided if there has been a break of two months or more in between administering the trial interventions to participants.

Participants are free to choose which practitioner they wish to see according to convenience (location, availability etc) however they are to be aware that there may be a “waitlist” for particular practitioners. Practitioners may also notify the research assistant or [name] when they are unable to take on new participants temporarily due to other commitments.

## Therapeutic intervention 2: Auricular Electro-acupuncture stimulation (AEA)

### Acupuncture rationale

#### Style of acupuncture

The intervention in this study is auricular electro-acupuncture using a fixed protocol that is informed by both Chinese medical and medical acupuncture principles.

#### Reasoning for treatment provided

No Chinese medicine diagnosis is required. The acupuncture points are chosen based on a literature review and expert consensus on the traditional and physiological indications of the points.

#### Extent to which treatment will be varied

There is to be no variation in treatment.

### Details of needling

#### Number of needle insertions per subject per session

Each subject will receive needling at three acupuncture points on the concha of one ear only. The ears are to be alternated between visits unless there is any objection from the participant.

#### Names of points to be used

The core acupuncture points on the concha of the ear to be used are the Stomach, Appetite Control, and Thalamus points.

#### Depth of insertion and response sought

No *de qi* sensation is to be sought. Needles are to be inserted superficially and not into the cartilage of the ear.

#### Needle stimulation

The Neurova device will be attached after insertion of the needles to the ear, according to the manufacturer's instructions (See Appendix 15).

#### Needle retention time

Needles are retained for up to 96 hours. The participant is to remove the Neurova device by gently pulling out the needles and disconnecting the wire. The needles are then placed into a provided sharps container. Gentle pressure is applied with a cotton ball if there is any bleeding. Participants can remove the device before 96 hours if they experience significant discomfort. Participants bring the sharps container back to the post-intervention visit for adequate biological hazard waste disposal through NICM laboratories.

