#### Blinding

Investigators (outcome assessors and investigators involved in statistical analysis) are blinded to treatment allocation but treating acupuncturists and participants are not.

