#### Post-intervention visit

At the post-intervention visit which takes place after the participant has completed all her acupuncture treatments, the participant completes the same outcome measures as at the baselinepre-intervention visit but without the demographic/medical questionnaire.

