## Anthropometric measures and blood pressure

We will measure weight on a calibrated digital scale, waist and hip circumference at the baseline and follow-up clinic visits. We will measure height by stadiometer at the baseline clinic visit. Blood pressure is measured while sitting quietly and after resting quietly for a few minutes, and with both feet on the ground, using an Omron digital automatic standard blood pressure monitor. A large cuff is used if required. Blood pressure on both arms will be obtained initially and the higher blood pressure of the two will be used. Three measurements will be taken, and the average of the last two measurements is recorded. If there is >10mm/Hg or >6mm/Hg difference in systolic or diastolic blood pressure respectively, the participant is asked to rest quietly for five minutes and blood pressure measurement is repeated ([48](#_ENREF_48)).

Anthropometric measures and blood pressure will be measured according to standard procedures as outlined in http://www.cdc.gov/NCHS/data/nhanes/nhanes_07_08/manual_an.pdf

Data will be entered by the Research assistant into the Redcap database.

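### AEA participants are told to bring an arm-identifying sharps container to the outcome visit, with nothing in place to keep it from the assessors whom the protocol declares blinded

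*Protocol*

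**What the plan says.** The AEA part of the protocol (section 6.2.2, Needle retention time) has each woman remove the device and its needles herself, up to 96 hours after insertion. It continues: "The needles are then placed into a provided sharps container". It then gives the return route: "Participants bring the sharps container back to the post-intervention visit for adequate biological hazard waste disposal through NICM laboratories".

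Section 7.1.1 says of that same visit that "the participant completes the same outcome measures as at the baselinepre-intervention visit". Section 8.1 adds: "We will measure weight on a calibrated digital scale, waist and hip circumference at the baseline and follow-up clinic visits". Appendix 1 shows the visit, at week 12, as the only clinic assessment after baseline.

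On masking, section 5.5.1 (Blinding) states: "Investigators (outcome assessors and investigators involved in statistical analysis) are blinded to treatment allocation but treating acupuncturists and participants are not".

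**The concern.** An object that only one arm is described as holding is directed, by a written participant instruction, to the visit at which supposedly blinded staff take the follow-up measurements. Participants and acupuncturists are openly unblinded, so assessor blinding is the main stated protection for measures that depend on the observer. If an assessor sees the container, that protection is lost for AEA women at their only follow-up clinic assessment.

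Two of the three pairwise comparisons involve AEA: against body acupuncture and against lifestyle alone. The synopsis wants effect sizes across all three arms, to inform a fully powered trial. A return procedure that undermines masking could distort those estimates and could be carried into the larger study.

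**Working it through.** The plan gives no figure to reproduce on this point. The check is a comparison of sections.

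1. **Is the container due at the outcome visit?** Yes. Section 6.2.2 (AEA) sends it to the post-intervention visit, and section 7.1.1 repeats the baseline measures there.

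2. **Does it mark a single arm?** Yes, on what is described. For body acupuncture, section 6.1.2 says "Needles are retained for 30 minutes", within a clinic session, and mentions no take-home container. The control arm (section 6.3) receives lifestyle coaching only and has no needles. A woman carrying the container is therefore identifiable as AEA. A woman without one could be in either of the other two arms.

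3. **Are assessors declared blinded?** Yes, in section 5.5.1.

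4. **Is there a safeguard between container and assessor?** None is stated: no named receiver, no hand-over before measurement, no instruction to conceal it.

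5. **Does the assessor receive or see it?** The protocol does not say. This step is an inference from steps 1 to 4.

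6. **How many women?** Section 4.1 randomises 13 + 13 + 13 = 39. The AEA share is 13/39, or one third. Among those to be analysed it is 10/30, also one third. This is the fraction of women whose arm could be revealed. It does not measure bias.

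7. **Which measures are exposed?**

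| Measure | Where and how taken | Exposure |
| --- | --- | --- |
| Waist and hip circumference | Clinic visit, by hand (8.1) | Real |
| Ferriman-Gallwey score | Research assistant and/or the woman herself (section 8, Clinical Hyperandrogenism) | Real when staff score it |
| Weight | Calibrated digital scale (8.1) | Low |
| Blood pressure | Automatic monitor, three readings, mean of the last two, numeric repeat thresholds (8.1) | Low |
| Glucose, insulin, androgens | External pathology centres (8.2) | Low |
| Accelerometry, menstrual diary, coaching data | Outside the clinic visits (7.1.1) | Not through this route |

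8. **Who might the assessor be?** Under section 5.5.1 (Implementation) the research assistant opens the envelope and books the first treatment. Under section 8.3 a research assistant records the ECG, and the research assistant may also score hirsutism. If one person does all this, she knows all three arms from randomisation and the container tells her nothing new. If a different person assesses, the container can reveal AEA.

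**The case against.** The strongest reply is that the container is not the main threat to blinding. On the roles as described, the research assistant may already know every allocation, so changing the return route alone would not make section 5.5.1 true. That stands, and it is why the fix below has two parts. It does not make the instruction sound: if the sponsor appointed an independent assessor, the instruction would still expose that person to AEA allocation.

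A second reply is that other cues exist at the same visit. Appendix 1 places adverse-event recording and the exit survey there, and the survey asks about body acupuncture and AEA. Whether an assessor sees these is also unstated. This is fair, but the container differs in being an arm-specific object that the protocol itself directs to the visit.

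A third reply is that the trial is open-label with feasibility endpoints as primary, so only secondary outcomes are touched. That also stands, and it limits the weight of the point.

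A reader might go further and infer that the assessor certainly learns who is in the AEA arm, or that every follow-up outcome is compromised. The protocol supports neither. It does not say who takes the container or when in the visit, and several outcomes are collected elsewhere. Nor is blood pressure a good example of a discretionary measurement, since its repeat rule has fixed numeric triggers.

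**Conclusion.** The point holds as a weakness in the blinding arrangement. The AEA return instruction creates a foreseeable and unprotected route to unblinding for any assessor not already unblinded by opening the envelope. It concerns one arm of three, at the only follow-up clinic visit. The consequence is confined mainly to waist and hip circumference and a staff-scored Ferriman-Gallwey score, which are secondary outcomes. The direction and size of any bias cannot be derived from the document.

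The conclusion rests on two assumptions: that no other arm is given a take-home container, as the protocol's silence indicates, and that no hand-over arrangement exists in documents not shown. It is worth correcting because the change is trivial and the study is meant to test procedures for a larger trial.

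**What to change.** Amend section 6.2.2 (AEA, Needle retention time) and the participant instructions so that the container is left in an opaque bag at reception, or with existing staff who do not assess outcomes, before the woman meets the assessor. Add that neither the container nor the device is to be brought into the assessment. Disposal through the institute's laboratories is unchanged. Returning containers at the last treatment session would not be enough, because the final needles may stay in for up to 96 hours after it.

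Separately, reconcile section 5.5.1 (Blinding) with section 5.5.1 (Implementation), section 8.3 and the Clinical Hyperandrogenism text. Either the person who opens the envelope does not take the observer-dependent measures, or the blinding statement is limited to the roles and outcomes for which it is true.

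The container change costs one sentence in each document and a drop-off point. Separating the roles may need some reallocation of staff tasks; limiting the blinding statement needs only a wording change.

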#### Needle type

Needles are surgical grade titanium, sterile and disposable and approximately 6mm in length.

### Treatment regimen

#### Treatment frequency and duration

Women allocated to the AEA group will receive a total of 6 treatments of acupuncture over 12 weeks (twice a week for the first two weeks, then fortnightly for four treatments).

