| **Exclusion Criteria:** | - Planning to conceive within the next 3 months - Needle acupuncture in the previous 3 weeks - Unable to provide informed consent. - BMI >40 - anticoagulant use - pacemaker use - immunocompromise - valvular heart disease - Currently breastfeeding or have ceased breastfeeding within the past 6 weeks ( a waiting period may apply) |
| **Dosage Regimen/Duration of Treatment:** | 12 treatments of acupuncture over 12 weeks, twice a week for 4 weeks then fortnightly after |
| Investigational Product/Therapy 1: | Acupuncture and telephone-based lifestyle interventions |
| Investigational Product/Therapy 2: | Auricular Electro-acupuncture (AEA) stimulation and telephone-based lifestyle interventions |
| Control Group: | Telephone-based health coaching |
| **Study Procedures:** | The majority of outcomes will be completed at the pre and post intervention visit. Participants will wear an accelerometer at -1 and 11 weeks for 5-7 days and will complete a menstrual calendar. |
| **Statistical Analyses:** (Brief Description) | Descriptive statistics for primary endpoint. |

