## Endpoints

### Primary Endpoint

Recruitment, retention and adherence rates; credibility; acceptability; and safety over the recruitment and intervention periods.

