# Study Population

## Number of Participants

We aim to analyse 30 participants by the end of treatment. Allowing for a 25% dropout rate which has been reported in similar studies, we will randomise 39 women (13 to real acupuncture, 13 to AEA and 13 to lifestyle alone).

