#### Dealing with missed sessions

At the time of enrolment, participants are to be made aware of the nature of their commitment over the twelve week treatment period and encouraged to notify the research office, [name] or the treating practitioner as soon as a break in treatment is foreseen. If treatments are missed, all attempts will be made to complete ten treatments within the eight weeks, providing there is at least a 2 day interval between treatments A break in the intervention schedule may be unavoidable, due to illness or holiday. If the acupuncturist becomes aware that a break of more than two weeks is likely, they will be instructed to liaise with [name] for advice on how to deal with this. [name] or the research assistant will liaise with the participant to determine the cause of missed sessions and will attempt as much as possible to implement appropriate measures to minimise further breaks in between treatments.

As analysis will be by intention-to-treat (that is, all data will be analysed even if a participant has dropped out from the trial), a minimum number of treatment sessions to meet the protocol has not been specified.

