#### Pre-intervention/ Baseline visit

The purpose of the baseline visit is to obtain informed consent, collect baseline and demographic measures, randomise the participant, and organise the acupuncture treatments for the participant.

*Informed consent*

If the research assistant is not a practising acupuncturist, the participant will be telephoned by [name], an acupuncturist and researcher, in order to provide details about the acupuncture treatment and answer any queries about acupuncture. This is essential so that the participant can provide informed consent after understanding the risks and benefits of acupuncture treatment. This telephone call will take place prior to the baseline clinic visit.

During the clinic visit, which will take place at the National Institute of Complementary medicine, Campbelltown Campus, Western Sydney University, the participant will meet with the research assistant to provide informed consent.

*Baseline and demographic/medical measures*

The participant will have baseline outcome measures taken as per the following section on Data Collection. Briefly they include:

- Anthropometric measures and blood pressure
- Surveys on quality of life, anxiety and depression, weight self-efficacy, and internal locus of control.
- Measures of insulin resistance by blood tests collected by Laverty Pathology
- Testosterone, Free testosterone and Free Androgen Index collected by Laverty Pathology
- Clinical Hyperandrogenism as assessed by the Ferriman Gallwey score
- Heart rate using ECG monitoring at Headbox laboratory on the WSU Campbelltown Campus and also using a hand-held ambulatory monitor at the same time

Participants will also provide demographic and medical history details.

*Randomisation*

Participants will be assigned a randomisation ID number.

*Acupuncture treatments*

Participants are provided with information about the acupuncture treatments, will choose a treating acupuncturist for the intervention, and the research assistant will organise the participants’ acupuncture treatments according to the schedule.

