# Data Collection

Data on recruitment, retention, adherence and acceptability rates will be entered into Redcap clinical trial management software. These are defined as:

1. Recruitment rates (number of enquiries and number of enrolments per month of active recruitment; percentage conversion to enrolment measured as n enrolled/n of enquiries, and n enrolled/n potentially eligible);
2. Retention rate (n completing 12 week intervention and outcome measures/n enrolled)
3. Adherence rates (n completing at least 8 of 11 acupuncture treatments and 4 of 6 Neurova treatments; n of hours of wear of the Neurova^TM^ device/percentage of women who wore the device for the prescribed 96 hr duration; n completing all recommended phone calls with the GHS);
4. Acceptability is measured using an exit survey which includes questions on perceived benefits of body acupuncture, AEA, and health coaching, perceived detriments of being in the trial, likelihood of recommending the study to family or friends measured on a 5 point Likert scale ranging from “I would definitely participate/recommend it” to “I would definitely not participate/recommend it”;

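### The AEA visit pattern adds up to 8 sessions, not the stated 6 on which the adherence cut-off rests, and the missed-session target of ten in eight weeks fits neither acupuncture arm

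*Protocol*

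**What the plan says.** **AEA arm.** Section 6.2.3 (Treatment frequency and duration) prescribes "a total of 6 treatments of acupuncture over 12 weeks (twice a week for the first two weeks, then fortnightly for four treatments"). Section 8 (Data Collection, item 3) counts adherence as "n completing at least 8 of 11 acupuncture treatments and 4 of 6 Neurova treatments".

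**Body acupuncture arm.** Section 6.1.3 states 11 treatments over 12 weeks, given "twice a week for the first two weeks, weekly for four weeks, then fortnightly for 3 treatments".

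**Missed sessions.** Sections 6.1.3 and 6.2.3 carry the same instruction: if sessions are missed, "all attempts will be made to complete ten treatments within the eight weeks". Both paragraphs also refer to a twelve-week treatment period.

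**Synopsis.** The dosage line reads "12 treatments of acupuncture over 12 weeks, twice a week for 4 weeks then fortnightly after" and gives no separate AEA regimen.

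**Use of the count.** Section 2.2.1 lists as primary endpoint "Recruitment, retention and adherence rates; credibility; acceptability; and safety over the recruitment and intervention periods". Section 7.1.1 (Baseline visit) has the research assistant organise the "acupuncture treatments according to the schedule". Section 4.1 plans "13 to AEA and 13 to lifestyle alone".

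**The concern.** The AEA sentence contains two different courses of treatment. The total and the bracketed pattern cannot both be followed, and the person who books the visits is told to work from a schedule. Appendix 1 does not settle it, because its intervention rows are blank and it has no column for sessions after the first treatment.

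Two things are at stake. The first is dose: each AEA session leaves needles in the ear for up to 96 hours (section 6.2.2). The second is the meaning of a primary endpoint: a cut-off of 4 sessions is a different standard against a course of 6 than against a course of 8. The trial is meant to inform a larger one, so the AEA adherence rate is one of its main products.

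The make-up target is a separate error. It names a number of sessions and a period that belong to neither arm.

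**Working it through.** Every check is a session count, so each must match exactly. One assumption is made: the first fortnightly visit falls two weeks after the preceding block ends.

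**Body arm (section 6.1.3), as a control**
- 2 × 2 + 1 × 4 + 3 = 11. The stated 11 is reproduced.
- Due by week 8: 4 + 4 + 1 = 9.

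**AEA arm (section 6.2.3)**
- As printed: 2 × 2 + 4 = 8, at weeks 1, 1, 2, 2, 4, 6, 8 and 10. The stated 6 is not reproduced.
- Due by week 8 as printed: 4 + 3 = 7.
- Patterns that do give 6:
  - one a week for two weeks, then four fortnightly (2 + 4), at about weeks 1, 2, 4, 6, 8 and 10;
  - two in a single week, then four fortnightly (2 + 4);
  - two a week for two weeks, then two fortnightly (4 + 2), ending near week 6.

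**Adherence cut-off (section 8)**
- Against 6: 4/6 = 67%. Against 8: 4/8 = 50%. Body arm, for comparison: 8/11 = 73%.
- Fourth AEA session: end of week 2 as printed; about week 6 on the first of the three patterns above.
- Two-thirds of 8 is 5.3, so 6 of 8 (75%) is the smallest count that keeps the present share.
- Illustration only, assuming each session is attended independently with the same probability:

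| Attendance probability | At least 4 of 6 | At least 4 of 8 |
| --- | --- | --- |
| 0.5 | 0.34 | 0.64 |
| 0.7 | 0.74 | 0.94 |
| 0.8 | 0.90 | 0.99 |

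**AEA dose**
- Applications for 13 women: 13 × 6 = 78 or 13 × 8 = 104, a difference of 26.
- Maximum wear per woman: 6 × 96 = 576 h or 8 × 96 = 768 h.

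**Missed-session target of 10 in 8 weeks**
- AEA: 10 − 6 = 4 above the stated total; 10 − 8 = 2 above the pattern's total.
- Body arm: 9 sessions are due by week 8 and 11 in all, so 10 matches neither.

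**Synopsis**
- 2 × 4 + 8/2 = 12. This adds up by itself but conflicts with 11 in section 6.1.3. It has no bearing on the AEA denominator.

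**The case against.** The count itself is not in dispute. The case on the other side is about consequence.

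- **Only one adherence measure is affected.** Section 8 also lists hours of device wear, the share of women wearing the device for the full 96 hours, and completed coaching calls. This stands: the problem is confined to the session count. Hours of wear could expose a low dose if they are totalled per woman, which the section does not say.
- **Meeting the cut-off early is partly a matter of front-loading.** On the 4 + 2 pattern, 4 of 6 is also reached by the end of week 2. This stands as a caution: the week-2 versus week-6 contrast depends on which repair is chosen. The 4 + 2 pattern fits a 12-week course poorly, so 2 + 4 remains the more plausible reading. The fall from 67% to 50% does not depend on that choice.
- **The make-up text is a best-efforts instruction that applies only after a missed session.** The identical wording in both arms suggests carried-over text, and nobody is likely to read it as ordering extra device applications. That is fair, and over-treatment is not shown. The text still gives staff an unusable target.
- **It is not known that the pattern, rather than the total, would be booked.** True. The practitioner training manual is not at hand, and confusion in practice is not claimed.
- **Little depends on the figure.** Adherence is described, not tested (section 9.2). No test, sample size or progression rule uses the count, no minimum number of sessions is required, and each treatment is recorded on a Case Report Form (section 6.2.4). This limits the severity. The forms show what was delivered, however, and cannot say whether 6 or 8 was planned.

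**Conclusion.** The point holds. The AEA pattern gives 8 sessions against a stated 6, and the ten-in-eight-weeks target matches no regimen in the protocol. A total of 6 is better supported, because it appears in both section 6.2.3 and section 8, but the document does not settle it and the sponsor must.

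If the printed pattern is booked, the AEA session cut-off weakens from 67% to 50% of the course, and up to 26 more device applications are given than a total of 6 implies. The timing figures rest on the assumed placing of the first fortnightly visit and, for week 6, on the weekly 2 + 4 repair. The error should be fixed because it leaves a device dose and one measure within a primary endpoint ambiguous. It does not threaten the sample size or any inferential result. The synopsis mismatch (12 against 11) is a separate, smaller correction.

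**What to change.** 1. The sponsor confirms the AEA total.
   - **If 6:** correct the pattern in section 6.2.3, for example to one session a week for two weeks followed by four fortnightly sessions, and keep 4 of 6 in section 8.
   - **If 8:** change the total in section 6.2.3 and reset the cut-off in section 8. 6 of 8 is the smallest count that keeps at least two-thirds.
2. In both missed-session paragraphs, replace the target with that arm's own total within 12 weeks: 11 for body acupuncture and the confirmed number for AEA.
3. Align the synopsis to 11 body sessions, and add an AEA line so that the two regimens are not confused.
4. For women already treated, take the number of sessions delivered from the per-treatment Case Report Forms.

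**Cost.** If the total is 6, this is a wording amendment needing ethics committee approval (section 12.1), with no added participants or treatments. If it is 8, the same amendment also changes the adherence cut-off and means up to 13 × 2 = 26 more AEA applications than a total of 6 implies.
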